# Comparison of 8 weeks standard treatment (rifampicin plus clarithromycin) *vs.* 4 weeks standard plus amoxicillin/clavulanate treatment [RC8 *vs.* RCA4] to shorten Buruli ulcer disease therapy (the BLMs4BU trial): study protocol for a randomized controlled multi-centre trial in Benin

**DOI:** 10.1186/s13063-022-06473-9

**Published:** 2022-07-08

**Keywords:** Buruli ulcer, Skin neglected tropical disease, Treatment shortening, Non-inferiority, Drug combination, Amoxicillin, Clavulanate, Pharmacokinetics, Bacterial clearance

## Abstract

**Background:**

Buruli ulcer (BU) is a neglected tropical disease caused by *Mycobacterium ulcerans* that affects skin, soft tissues, and bones, causing long-term morbidity, stigma, and disability. The recommended treatment for BU requires 8 weeks of daily rifampicin and clarithromycin together with wound care, physiotherapy, and sometimes tissue grafting and surgery. Recovery can take up to 1 year, and it may pose an unbearable financial burden to the household.

Recent in vitro studies demonstrated that beta-lactams combined with rifampicin and clarithromycin are synergistic against *M. ulcerans*. Consequently, inclusion of amoxicillin/clavulanate in a triple oral therapy may potentially improve and shorten the healing process.

The BLMs4BU trial aims to assess whether co-administration of amoxicillin/clavulanate with rifampicin and clarithromycin could reduce BU treatment from 8 to 4 weeks.

**Methods:**

We propose a randomized, controlled, open-label, parallel-group, non-inferiority phase II, multi-centre trial in Benin with participants stratified according to BU category lesions and randomized to two oral regimens: (i) Standard: rifampicin plus clarithromycin therapy for 8 weeks; and (ii) Investigational: standard plus amoxicillin/clavulanate for 4 weeks. The primary efficacy outcome will be lesion healing without recurrence and without excision surgery 12 months after start of treatment (i.e. cure rate). Seventy clinically diagnosed BU patients will be recruited per arm. Patients will be followed up over 12 months and managed according to standard clinical care procedures. Decision for excision surgery will be delayed to 14 weeks after start of treatment. Two sub-studies will also be performed: a pharmacokinetic and a microbiology study.

**Discussion:**

If successful, this study will create a new paradigm for BU treatment, which could inform World Health Organization policy and practice. A shortened, highly effective, all-oral regimen will improve care of BU patients and will lead to a decrease in hospitalization-related expenses and indirect and social costs and improve treatment adherence. This trial may also provide information on treatment shortening strategies for other mycobacterial infections (tuberculosis, leprosy, or non-tuberculous mycobacteria infections).

**Trial registration:**

ClinicalTrials.gov NCT05169554. Registered on 27 December 2021.

**Supplementary Information:**

The online version contains supplementary material available at 10.1186/s13063-022-06473-9.

## Background

Buruli ulcer (BU) is a chronic debilitating skin and soft tissue mycobacterial infection that without treatment frequently progresses to massive ulceration. The greatest burden falls on children below 15 years in sub-Saharan Africa, accounting for at least 50% of those affected by BU [1]. In 2019, Africa presented the highest number of cases (86.2%) among the new reported cases (2260) [2]. This skin neglected tropical disease (NTD) generally affects poor communities in remote rural areas with limited access to health services. Although mortality is low, permanent disfigurement and disability are high, occurring in up to 25% of the cases [3].

BU is caused by *Mycobacterium ulcerans* but transmission patterns remain unknown, and thereby, early diagnosis and treatment are crucial to minimize morbidity costs and prevent long-term disability. Before 2004, surgical excision and skin grafting remained the mainstay of BU treatment [4–6] until clinical evidence showed the effectiveness of rifampicin-streptomycin [7]. Serious adverse events (SAEs) associated with the injectable streptomycin and the lack of an efficacious oral treatment, however, remained one of the main obstacles to decentralizing care in rural areas. Since 2017, the World Health Organization (WHO) recommends an 8-week completely oral daily combination therapy of rifampicin-clarithromycin (RIF/CLA) [8]. However, access to medicines is difficult, and the need of hospitalization for treatment impacts a patient’s household income and compromises adherence to the 8-week antibiotic course [9–11]. Similar to tuberculosis (TB), RIF is the cornerstone drug for BU therapy, showing a direct relation between dose increase and therapy efficacy [12] due to its bactericidal and sterilizing activity [13]. High-dose RIF studies suggest that BU treatment could be shortened if RIF dose was increased [13, 14]. Nevertheless, this approach raises concerns due to high-dose RIF-related hepatotoxicity and feasibility of its implementation in the clinical practice. It would be thus desirable to maintain the current dose and improve RIF efficacy without compromising tolerability and toxicity; this could be achieved using RIF in combination with synergistic partners [15–17]. Recent studies from partners of this Consortium showed in in vitro studies that beta-lactams strongly increased the activity of RIF and CLA against *M. ulcerans* [16]. These observations were further confirmed by time-­kill kinetics (*unpublished data, manuscript under preparation, BLMs4BU Consortium*).

Among all beta-lactams, we focused on amoxicillin/clavulanate (AMX/CLV), which is oral, suitable for the treatment of children, pregnant women, and adults and with a long track record of clinical efficacy and safety [18]. Due to its rapid bactericidal activity, AMX/CLV would be effective at reducing initial bacterial burden, paradoxical responses [19], local levels of the immune-suppressive mycolactone toxin, and allowing recovery of the host immune response to clear remaining bacteria [14]. Furthermore, the sterilizing activity of synergistic combinations of beta-lactams and RIF could target the remaining persistent populations ultimately allowing for a potentially shorter duration of treatment and healing periods [15, 20].

A shortened, highly effective, all-oral regimen based on already approved drugs is thus urgently needed to improve care for this NTD by reducing both duration of treatment and time to healing for all type of lesions after therapy completion. This will ultimately reduce the associated indirect and social costs, and barriers to access therapy. Moreover, developing more effective and accessible NTD therapeutic strategic will up thrust the lifespan and lifestyle of the socioeconomically deprived areas affected by this disease. Therefore, in this study, we propose the combination of AMX/CLV with current oral BU therapy, RIF/CLA, as a new BU therapy with the potential of treatment shortening and ready implementation in the field. For this purpose, a Phase II clinical trial will be conducted in Benin.

### Aims of the study

#### Primary objective

The primary objective is to demonstrate the non-inferiority of 4-week co-administration of AMX/CLV with RIF/CLA compared to the standard 8-week RIF/CLA in cure rates at 12 months post initiation of treatment, thus supporting reduction of BU treatment from 8 to 4 weeks.

#### Secondary objectives

To test the hypothesis that 4-week combination therapy of RIF plus CLA plus AMX/CLV (RCA4) could improve the median bacterial clearance rate over the currently WHO-recommended 8-week RIF plus CLA (RC8) therapy,To investigate whether a hypothetical increase in the median bacterial clearance rate due to the addition of AMX/CLV correlates with a reduction in the median time to healing of the BU lesions,To explore the effect of AMX/CLV on RIF/CLA pharmacokinetics (PK), andTo characterize the population PK (POPPK) of RIF and AMX in BU patients randomized in the investigational regimen (RCA4).

### Methods/design

#### Study design

BLMs4BU study is a Phase II, randomized, controlled, open-label, parallel-group, non-inferiority, multi­centre trial, with two treatment arms:Standard [RC8]: RIF plus CLA (RC) therapy for 8 weeks; andInvestigational [RCA4]: standard (RC) plus AMX/CLV (A) for 4 weeks.

The flow chart of the clinical trial study design and timelines are depicted in Figs. 1 and 2. In addition, a PK and microbiology study will be also performed in a complementary manner. Details of ethics approval are provided at the end of the manuscript.

**Fig. 1 Fig1:**
[figure not shown]
Flow chart of sampling, recruitment and timelines of the clinical trial

**Fig. 2 Fig2:**
[figure not shown]
Schedule of screening, randomization, interventions and assessment of the patients in the BLMs4BU study. AEs, adverse events; BUFLS, Buruli Ulcer Functional Limitation Score; FNA, fine-needle aspiration; M, month; HIV, human immunodeficiency virus; PCR, polymerase chain reaction; RC8, 8 weeks of rifampicin-clarithromycin; RCA4, 4 weeks of rifampicin-clarithromycin plus amoxicillin/clavulanate; SAEs, serious adverse events; W, week. *PK analysis (blood samples). It will be performed between days 7 and 14 after starting the treatment, prior to the second daily dose of CLA and AMX/CLV. Sampling times will include a pre-dose at time 0 (within 10 min pre-dose) and at times 0.5, 1, 1.5, 2, 2.5, 3, 5, 7.5, and 10 h post-dose

#### Study setting

The main study will be conducted in three clinical sites that are Centers of Detection and Treatment of Buruli Ulcer (Centre de Dépistage et de Traitement de l’Ulcère de Buruli, CDTUB) in Benin, located in the towns of Pobè, Allada and Lalo, in the south of the country, where BU is endemic (Fig. 3). PK and bacterial clearance sub-studies will be performed only at the Pobè treatment centre.

**Fig. 3 Fig3:**
[figure not shown]
Location of the Lalo, Allada, and Pobè clinical sites in Benin, where the study will be conducted. Figure made with mapchart.net [21]

#### Eligibility criteria

All patients (both genders) aged ≥ 5 years and ≤ 70 years with a very likely or likely new clinical diagnosis of BU according to WHO scoring criteria (Fig. 4) [22–24] (all categories: I, II, III) and normal electrocardiogram (ECG) at baseline. Patients meeting inclusion criteria will be invited to participate and enrolled in the study. Non-inclusion criteria are listed in Table 1.

**Fig. 4 Fig4:**
[figure not shown]
WHO clinical diagnosis scoring criteria

**Table 1 Tab1:** Overview of inclusion and exclusion criteria in the BLMs4BU study

Inclusion criteria
Patients must fulfil the following criteria:
•Age of ≥ 5 years and adults ≤ 70 years
•New clinical diagnosis of BU (all categories: I, II, and III)
•Normal ECG
**Exclusion criteria**
Patients with any of the following criteria are not eligible:
•Children < 5 years and adults > 70 years
•Children in foster care
•Patients weighing less than 11 kg
•Pregnancy positive (urine test: beta-HCG positive)
•Previous treatment of Buruli ulcer, tuberculosis, or leprosy with at least one of the study drugs
•Patients with diagnosed leprosy or tuberculosis disease
•Hypersensitivity to at least one of the study drugs or to any of the excipients
•History of a severe immediate hypersensitivity reaction (e.g. anaphylaxis) to another beta-lactam agent (e.g. a cephalosporin, carbapenem, or monobactam)
•History of jaundice/hepatic impairment due to amoxicillin/clavulanic acid or rifampicin
•Patients with history of treatment with macrolide or quinolone antibiotics, anti-tuberculosis medication, or immuno-modulatory drugs including corticosteroids within 1 month
•Patients currently receiving treatment with any drugs likely to interact with the study medications, i.e. anticoagulants, cyclosporine, phenytoin, or phenobarbitone. Users of oral contraceptives should be notified that such contraceptive is less reliable if taken with rifampicin; additional (mechanical) contraceptive methods will be discussed with the study participant
•Patients with HIV co-infection
•Patients with QTc prolongation > 450 ms on ECG or on other medication known to prolong the QTc interval. In this case, if suspected of BU disease, patients will be offered 8-week rifampicin plus streptomycin therapy
•Patients unable to take oral medication or having gastrointestinal disease likely to interfere with drug absorption
•Patients with history or having current clinical signs of ascites, jaundice, myasthenia gravis, renal dysfunction (known or suspected), diabetes mellitus, and severe immune compromise, or evidence of tuberculosis, or leprosy; terminal illness (e.g. metastasized cancer), haematological malignancy, chronic liver disease, abnormal liver function test, and coronary artery disease, or any other condition that would preclude enrolment into the study in the study physician’s opinion
•Evidence of a clinically significant (as judged by the Investigator) condition or abnormality (other than the indication being studied) that might compromise safety or the interpretation of trial efficacy or safety endpoints
•Patients with known or suspected bowel strictures who cannot tolerate clarithromycin
•Patients with a mental health condition that is likely to interfere with compliance with the study protocol in the opinion of the study physician
•Patients (or parent/legal representative) who are not willing to give informed consent or withdrawal of consent
•Specific exclusion criteria for the PK sub-study are patients less than 15 years old or less than 40 kg or with renal impairment with a creatinine level higher than the normal one in Benin (7–14 mg/L)
•Patients who cannot confirm the absence of previous BU treatment or with potential difficulties to be followed up

### Procedures and measurements

#### Screening and informed consent

Information, education, and communication campaigns and active case finding will be performed weekly in the communities during the study period together with mobile medical consultations of skin diseases which will be implemented too. These activities which will involve community volunteers, teachers, nurses from decentralized centres, and traditional healers, and they will help for detection of BU cases and referral to the BU health centres. Patients suspected to have BU will be recruited from villages covered by the different study sites participating in this trial: Pobè, Lalo, and Allada. During health promotion activities, people living in endemic villages will be encouraged to participate at workshops where information will be provided beforehand of the details and intentions of the study, and the benefits it might bring to them and the community at large. Culturally sensitive aspects of the protocol, especially testing for pregnancy and co-infection with human immunodeficiency virus (HIV) or TB will be discussed with community leaders in the villages.

Potential study participants will receive a unique study code number, kept with the site clinical investigator and the clinical study coordinators. They will also be informed about the importance of early reporting as well as their continuing participation to the end of the study.

At the study site, lesions will be clinically examined for compatibility with BU and scored according to WHO recommendations (Fig. 4) [22, 23] through consensus by the clinical investigators in each study site. Patients will also be assessed for eligibility by the site clinician, or health care worker delegate. If the lesion is clinically diagnosed as a very likely or likely BU lesion by the clinicians at the trial sites, after verbal and written explanation appropriate consent/assent by participants, and/or consent by their caregivers or legal representatives will be sought. The patient will be enrolled into the study only after informed consent has been obtained and forms are signed by both the study team member (Clinical Principal Investigator or deputy) and the study participant (sign or thumbprint, in case the participant is illiterate witnessed by an independent observer who is literate and is not part of the clinical trial team).

#### Assessment of the lesions

A full description of all lesions (including stage: ulcer, non-ulcer; lesion size and category; digital photography) will be obtained by the health care professional. The maximum diameter and the diameter at right angles to the maximum diameter line of the lesions will be measured using a transparent ruler, which will be disinfected between patients. The margins of the indurated area of the lesion determined by palpation and marked by a non-permanent marker will form the boundaries to be measured. In ulcerative lesions, these will be the margins of the skin defect and the indurated area. Digital photographs will be taken of all lesions as part of the documentation of clinical evolution. In addition, a questionnaire will be filled in to determine the Buruli Ulcer Functional Limitation Score (BUFLS) [24–28].

#### Laboratory evaluation

Blood and urine samples will be collected and laboratory analysis performed at the clinical sites. The specimens will be collected, transported, stored, and prepared according to local protocols. Blood will be stored at 2–8 °C before handling within the required time. Urine samples will be transported at room temperature and must be handled within 2 h after collection. If necessary, samples will be eventually destroyed by incineration.

The following tests will be performed: routine blood testing (clinical haematology including haemoglobin, white blood cells, and red blood cells; clinical chemistry in serum); urine test (routine urinalysis); blood HIV-testing (following counselling and once consent for HIV-testing is provided); assessment of the corrected QT (QTc) prolongation on ECG and; urine beta-human chorionic gonadotropin levels (hCG) for all females of child-bearing age (10–50 years) to rule out pregnancy.

Pregnancy test and HIV counselling and testing will be treated with strict confidentiality. Patients with a positive pregnancy test at screening will be not be enrolled in the study. The test result will firstly be discussed with the study participant (even if this person is below the age of 18 years) and, if agreed, with the parent or caretaker. The pregnancy test will be repeated at week 4 for all women of child-bearing age randomized in the RC8 group. If in this case the pregnancy test demonstrates pregnancy, the patient will be excluded from further participation in the trial but will continue on WHO-recommended antibiotic therapy and regular wound care follow-up procedures, according to the BU National Program (PNLLUB) guidelines for management of BU. Data collected prior to this will however be included in the analysis.

In addition, an aliquot of 2 mL of serum will be stored (− 20 °C) for future diagnostic test development and evaluation at treatment sites. Specific consent will be obtained for this. Samples will be stored anonymously at a central location for a minimum of 5 years and a maximum of 10 years after completion of the study, after which these specimens will be destroyed according to local guidelines and protocols. The potential use of the stored samples is included in the informed consent form. Nevertheless, further use of the samples will need to be approved by the Ethics Committee (EC) in Benin.

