#### Treatment

Two treatment regimens will be used in this clinical study protocol (Table 2):WHO-recommended standard (control): 8 weeks of rifampicin plus clarithromycin [8].Investigational: 4 weeks of rifampicin plus clarithromycin plus amoxicillin/clavulanate.

**Table 2 Tab2:** Clinical trial treatment cohort regimens

Treatment cohort	Dose	Posology	Treatment length
Standard arm: [RC8]	^**1**^Rifampicin 600 mg	Daily	8 weeks
	^**1**^Clarithromycin 500 mg	Twice daily	8 weeks
Investigational arm: [RCA4]	^**1**^Rifampicin 600 mg	Daily	4 weeks
	^**1**^Clarithromycin 500 mg	Twice daily	4 weeks
	^**2**^Amoxicillin/clavulanate 1000/125 mg	Twice daily	4 weeks

^1^Dose indicated are for a 60 kg adult and will be standardized according to patient body weight following the WHO guidelines [31]. Rifampicin (R), 10 mg/kg; Clarithromycin (C) 7.5 mg/kg

^2^Dose of amoxicillin/clavulanate (A) 1000/125 mg twice daily, which makes a total of 2000/250 mg/day, for patients over 40 kg, and 22.5/5.6 mg/kg twice daily, which makes a total of 45/11.25 mg/kg/day, for those equal and below 40 kg. For children, posology will be adapted to the age of the patient according to drug manufacturer indications. There are no current recommendations for the use of amoxicillin/clavulanate for BU infections. Those indicated above are recommended doses for complicated infections according to manufacturer indications

During the trial period of antibiotic treatment, patients will be either admitted to the hospital, or receive directly observed therapy at one of the participating satellite health centres. All RC8 or RCA4 treatment will be fully supervised by health care staff to avoid possible side effects (Table 3).

**Table 3 Tab3:** List of possible effects due to rifampicin, clarithromycin, and amoxicillin/clavulanate

	**Rifampicin**	**Clarithromycin**	**Amoxicillin/clavulanate**
More common	None	None	Nausea, vomiting, headache, diarrhoea, gas, stomach pain, skin rash or itching, white patches in your mouth or throat

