#### Discontinuation from the study medication

Patients who meet study eligibility criteria, give informed consent (or assent plus consent by caretakers) but who may not have completed the full treatment course of antibiotic therapy will be discontinued from the study medication for any one of the following reasons:Observation of rapid enlargement of the lesion despite drug treatment, and not attributed to a paradoxical response.Presence of SAE or adverse drug reaction of NIH/NCI Common Toxicity Criteria [33] grade 3 or 4 that prevent adherence to treatment.Need to use any drug with anti-mycobacterial activity or likely to interfere with interpretation of the results during the treatment period.Allergic reaction to a study drug.Observation of any new condition or situation (including pregnancy, major trauma, or severe immune compromise) developing during the trial, which in the judgement of the investigation team, may interfere with continued participation in the study.At the request of the subject / withdrawal of consent or assent.Non-compliance with scheduled follow-up visits.Non-compliance with medication.If the investigator considers that a patient’s health will be compromised due to AEs, SAEs, or a concomitant illness that develops after entering the study.

They will however be followed up for safety and included in the analysis.

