#### Procedures for withdrawal from the study

Subjects withdrawn from the study will not be replaced (5% drop out has been assumed for power calculations) but will be included in the analysis. Subjects who withdraw will be invited to continue attending study clinics for routine care and measurements and will be offered the standard of care according to the PNLLUB guidelines. Reasons for withdrawal will be recorded in the CRF and in the subjects’ medical notes and will be taken into account to prevent any potential loss of patients.

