#### Primary endpoint

The primary clinical efficacy endpoint is cure rate, i.e. proportion of patients with complete lesion healing without recurrence and without excision surgery 12 months after treatment initiation, in the PP PCR-positive population.

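### A positive week-4 pregnancy test, scheduled only in RC8, ends trial participation before the 12-month outcome and conflicts with the protocol's own rules on follow-up and analysis (minor)

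*Protocol article*

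**What the plan says.** *Laboratory evaluation* fixes a test and its consequence. The test: "The pregnancy test will be repeated at week 4 for all women of child-bearing age randomized in the RC8 group". The consequence of a positive result: "the patient will be excluded from further participation in the trial but will continue on WHO-recommended antibiotic therapy", with wound care under the national programme's guidelines. On data: "Data collected prior to this will however be included in the analysis". No matching test or exclusion is stated for RCA4.

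*Discontinuation from the study medication* names pregnancy in either arm. One listed reason is "Observation of any new condition or situation (including pregnancy, major trauma, or severe immune compromise) developing during the trial", where the investigation team judges that it may interfere with continued participation. The section closes: "They will however be followed up for safety and included in the analysis".

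*Procedures for withdrawal from the study* adds: "Subjects withdrawn from the study will not be replaced (5% drop out has been assumed for power calculations) but will be included in the analysis". Those who withdraw are also invited to keep coming for routine care and measurements.

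The primary endpoint is "proportion of patients with complete lesion healing without recurrence and without excision surgery 12 months after treatment initiation, in the PP PCR-positive population".

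**The concern.** The outcome that decides the trial is read 12 months after treatment starts. A rule that ends participation at week 4 and keeps only what was collected up to then leaves that outcome unobserved within the trial. It can be triggered by a scheduled test in one arm only, so whether a pregnant woman's outcome is recorded depends on her allocation. An analysis plan cannot recover an outcome that the protocol told the site not to collect.

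The protocol also gives sites incompatible instructions for one event. For an RC8 woman found pregnant at week 4, one section ends her participation and another keeps her in follow-up and in the analysis. The sections differ on drug treatment too: one continues antibiotics, the other lists pregnancy among reasons to stop study medication. In RC8 the study medication is itself the WHO-recommended standard, "8 weeks of rifampicin plus clarithromycin", so the two statements concern the same drugs unless the protocol says otherwise.

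**Working it through.** **1. The passages side by side, for a pregnancy known at week 4**

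| | Laboratory evaluation | Discontinuation from the study medication | Procedures for withdrawal |
|---|---|---|---|
| Applies to | RC8 women of child-bearing age | either arm, course not completed | either arm |
| Antibiotics | continue, WHO-recommended | study medication stopped, subject to the team's judgement | standard of care offered |
| Trial follow-up | ends | continues, for safety | invited for routine care and measurements |
| Data used | those collected before exclusion | included in the analysis | included in the analysis |

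An RCA4 woman pregnant at week 4 has reached the end of her 4-week course. The rule on stopping medication has little left to act on, and no stated rule removes her from follow-up. The handling of the month-12 outcome therefore differs by arm.

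**2. The plan's own sample size**

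Inputs from *Sample size*: cure 95.9% in both arms, margin 10 points, one-sided alpha 2.5%, power 80%.

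n per arm = (1.960 + 0.842)² × 2 × 0.959 × 0.041 / 0.10² ≈ 61.7, rounded up to 62. Allowing 5% loss: 62 / 0.95 = 65.3, so 66. Both match the protocol.

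**3. How many women**

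The document gives neither the share of females aged 10–50 nor a pregnancy rate. Assumed: 20–40% of the 66 RC8 patients, with 0.5–3% of these positive at week 4.

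- Low: 66 × 0.20 × 0.005 = 0.07. Chance of at least one: 1 − 0.995^13.2 = 6%.
- High: 66 × 0.40 × 0.03 = 0.79. Chance of at least one: 1 − 0.97^26.4 = 55%.

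**4. Power per lost RC8 outcome**

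Power = Φ(0.10 / SE − 1.96), with SE = √[0.959 × 0.041 × (1/n_RC8 + 1/62)].

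| RC8 evaluable | Power |
|---|---|
| 62 | 80.2% |
| 61 | 79.9% |
| 60 | 79.5% |
| 59 | 79.2% |

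Each lost outcome costs about 0.3 points.

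**5. What one woman does to the RC8 cure rate**

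Expected cures: 62 × 0.959 = 59.46, so about 2.5 failures.

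- Dropped, would have been cured: 58.46 / 61 = 95.8%, a fall of about 0.07 points.
- Dropped, would have failed: 59.46 / 61 = 97.5%, a rise of about 1.6 points.
- Kept but counted as not cured, otherwise an average patient: 0.959 × 61 / 62 = 94.35%, a fall of about 1.5 points, which favours non-inferiority of RCA4.

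The sign depends on her unobserved outcome and on how she is classified.

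**The case against.** Several points on the other side stand.

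- **The test is not arbitrary.** After week 4 only RC8 women still face study drug. A reader might take the one-arm test as the flaw. The regimen lengths explain it; only the consequence of a positive result is open to criticism.
- **The withdrawal section softens the conflict.** If a woman excluded at week 4 counts as withdrawn, she is in the analysis and is invited for measurements. But that invitation is addressed to those who withdraw, while *Laboratory evaluation* speaks of exclusion and limits the data to those already collected. The ambiguity remains.
- **The discontinuation section promises less than one might wish.** It offers follow-up for safety and inclusion in the analysis, and does not expressly promise the 12-month cure assessment. It still contradicts an end to participation.
- **The drug statements might be compatible.** She could formally leave study medication and receive antibiotics through the programme. The protocol does not say so.
- **The numbers are tiny.** The sample size already allows four losses per arm (66 to 62), and multiple imputation is planned as a sensitivity analysis.

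A reader might also infer that the randomised comparison is broken in both the per-protocol and ITT-E populations. The document does not support that. ITT-E membership needs only randomisation and one dose (plus PCR positivity for one of the sets), so she stays a member; what is at risk is her observed outcome. Her per-protocol status is unclear: the general definition requires study completion, while the PCR-positive definition mentions only major violations.

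**Conclusion.** The point holds as a minor one. *Laboratory evaluation* prescribes loss of the 12-month outcome under a rule that exists in one arm only, and it conflicts with two other sections on follow-up and analysis and with one of them on medication. This is a stated rule, not a detail left to an analysis plan.

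The size is small: fewer than one woman expected under the assumed shares, and about 0.3 points of power for each outcome lost. Those shares are assumptions, and Fig. 2, the visit schedule, could not be read here.

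A reader might infer a bias towards declaring RCA4 non-inferior. That follows only if excluded women are counted as not cured, which the protocol does not say; if they are dropped, the direction depends on outcomes nobody has seen. Nothing in the document links pregnancy at week 4 to lesion cure.

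**What to change.** Amend *Laboratory evaluation* so that a positive week-4 test does not end trial follow-up. With consent, the scheduled outcome assessments and lesion photographs continue to month 12, and she is analysed as randomised in the ITT-E sets (in the PCR-positive set if PCR-positive). State one rule, the same in both arms, for whether a pregnancy during the trial affects per-protocol membership.

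Reconcile *Laboratory evaluation*, *Discontinuation from the study medication* and *Procedures for withdrawal from the study*, including on whether study medication continues. That clinical choice is for the investigators, and no view is taken on it here.

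The cost is a short protocol amendment and continued trial visits for the rare woman affected. It should not be assumed that those visits happen anyway: the protocol refers to wound-care follow-up under national guidelines, which are not shown, and nothing establishes that this includes a month-12 visit or photographs.
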